## Abstract

**Background:**

Diabetic kidney disease (DKD) is one of the main complications of type 2 diabetes mellitus (T2DM). DKD is a known risk factor for end-stage renal disease, cardiovascular disease, and all-cause death. Effective intervention for early-stage DKD is vital to slowing down the progression of kidney disease and improve prognoses. Mobile health (mHealth) is reportedly effective in supporting patients’ self-care and improving glycemic control, but the impact of mHealth on DKD has yet to be shown.

**Objective:**

The purpose of this study is to evaluate the efficacy of standard therapy with the addition of a self-management support system, DialBetesPlus, in patients with DKD and microalbuminuria.

**Methods:**

This study is a prospective, randomized, open-label, multicenter clinical trial. The target population consists of 160 patients diagnosed with T2DM accompanied by microalbuminuria. We randomly assigned the patients to 2 groups—the intervention group using DialBetesPlus in addition to conventional therapy and the control group using conventional therapy alone. DialBetesPlus is a smartphone application that supports patients’ self-management of T2DM. The study period was 12 months, with a follow-up survey at 18 months. The primary outcome was a change in albuminuria levels at 12 months. Secondary outcomes included changes in physical parameters, blood test results (glycemic control, renal function, and lipid metabolism), lifestyle habits, self-management scores, medication therapy, and quality of life.

**Results:**

The study was approved in April 2018. We began recruiting patients in July 2018 and completed recruiting in August 2019. The final 18-month follow-up was conducted in March 2021. We recruited 159 patients and randomly allocated 70 into the intervention group and 61 into the control group, with 28 exclusions due to withdrawal of consent, refusal to continue, or ineligibility. The first results are expected to be available in 2021.

**Conclusions:**

This is the first randomized controlled trial assessing the efficacy of mHealth on early-stage DKD. We expect that albuminuria levels will decrease significantly in the intervention group due to improved glycemic control with ameliorated self-care behaviors.

**Trial Registration:**

UMIN-CTR UMIN000033261; https://upload.umin.ac.jp/cgi-open-bin/ctr/ctr_view.cgi?recptno=R000037924

**International Registered Report Identifier (IRRID):**

DERR1-10.2196/31061

## Introduction

The increase in type 2 diabetes mellitus (T2DM) worldwide is the primary cause of the increasing prevalence of end-stage renal disease (ESRD) [1]. The number of ESRD patients under renal replacement therapy is estimated to be more than 3 million worldwide and is projected to increase to more than 5 million people by 2030 [2]. Therefore, effective management of diabetic kidney disease (DKD) is essential, especially in the early stages. It has been demonstrated that albuminuria is one of the earliest detectible clinical manifestations of kidney disease and is a potent risk factor for ESRD and all-cause death [3,4]. Renin-angiotensin blockades are approved as a strategy to reduce urinary albumin excretion and are in widespread use [5,6]. Recently, glucagon-like peptide-1 analogs and sodium-glucose cotransporter-2 inhibitors have also been shown to slow the progression of DKD potentially [7,8]. Despite all these pharmacological interventions, the overall prevalence of DKD did not change significantly among US adults with diabetes from 1988 to 2014 [9]. Moreover, with 415 million patients with diabetes reported worldwide in 2015, the number is still increasing and is predicted to rise to 642 million by 2040 [10]. There is an increasingly urgent need for a more effective methodology to prevent the progression of DKD.

Modification of dietary and exercise habits is still one of the most fundamental therapeutic strategies. However, a sufficient support system for patients’ self-care has not been established. Whereas mobile health (mHealth) interventions supporting patients’ self-management have shown effectiveness in glycemic control of T2DM [11-14], the effects of mHealth on DKD have yet to be evaluated.

In 2015, over half of the people with diabetes worldwide lived in Southeast Asia or the Western Pacific Region. In Asia, it is estimated that the number of patients with diabetes will increase 1.8 times by 2040, and ESRD prevalence will rise sharply relative to other regions [2,10]. However, a population-based approach is also reported to decrease diabetes-related ESRD successfully [15,16]. mHealth might be a promising population-based approach, providing basic treatment and reliable information with easy accessibility at low cost.

We previously reported that the self-management support system DialBetics significantly improved glycemic control in T2DM patients, possibly due to improvement in diet and exercise [17,18]. We have since developed an updated system, DialBetesPlus, to investigate the effect of mHealth on DKD. In this study, we investigate the impact of DialBetesPlus on patients with DKD and microalbuminuria.

## Methods

### Study Design

This study is a prospective, randomized, open-label, multicenter clinical trial. The study was conducted at 8 hospitals located in Tokyo and Kanagawa, Japan (Textbox 1). We aimed to evaluate the efficacy of DialBetesPlus on microalbuminuria in T2DM patients. Figure 1 shows a flowchart of this trial. The intervention group used DialBetesPlus and conventional therapy for 12 months, while the control group was treated with conventional therapy alone. The primary outcome was a change in albuminuria levels in a first-morning void after 12 months. The final follow-up was in 18 months, 6 months after the 12-month intervention period.

List of trial institutions.The University of Tokyo HospitalYokohama City University HospitalYokohama City University Medical CenterYokohama Rosai HospitalSaiseikai Yokohamashi Nanbu HospitalFujisawa City HospitalChigasaki Municipal HospitalMitsui Memorial Hospital

**Figure 1 figure1:**
[figure not shown]
Protocol flowchart.

### Participants

We recruited patients who passed all the inclusion and exclusion criteria before randomization (Textbox 2). The criteria were designed to include T2DM patients experiencing the early stage of DKD without any restrictions on physical activity. Eligible participants had T2DM with microalbuminuria (30-299 mg/g creatinine), hemoglobin A_1c_ (HbA_1c_) of 6.5% or more, and an estimated glomerular filtration rate (eGFR) of 45mL/min/1.73m^2^ or more. We obtained written, informed consent from all the patients participating in this study. Prior to the randomization, all enrolled patients were asked to use DialBetesPlus for 2 weeks to confirm their ability to use the system and devices properly. Eligible participants were those able to use DialBetesPlus for over 7 days during the initial 2-week confirmation period. The participants were randomized into either the intervention or control group in a one-to-one fashion based on albuminuria levels, gender, and age. The research team consisted of diabetologists, nephrologists, pharmacists, dieticians, nurses, a laboratory technician, and technical support experts. While the team handled technical troubles and monitored usage of the system, the patients continued to consult their attending doctors about their general health status. If 7 days passed without any input into the system, an alert was sent to encourage the patient to resume providing input. If 3 weeks passed without a patient inputting any data, we defined the patient as a dropout. Participants with whom the study team has lost contact were also treated as dropouts. The criteria for study discontinuance were a serious adverse event, patient request for discontinuance, pregnancy, or the judgment of a lead physician.

Inclusion and exclusion criteria.

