### Data Collection

At registration, we collected information on patients’ background, albuminuria level in a first-morning void, physical parameters, medications, blood tests, food-log diaries, J-SDSCA, MMAS-8, and JP-ADDQoL. Follow-up visits were scheduled at 2 months (plus or minus 4 weeks), 6 months (plus or minus 6 weeks), 12 months (plus or minus 6 weeks), and 18 months (plus or minus 6 weeks). We collected and recorded information according to the schedule in Table 1. Even if the interventional treatment was discontinued, we collected as much information as possible with the consent of participants.

**Table 1 table1:** Assessment and follow-up schedule.

Assessments	Follow-up period				
	Registration	2 months	6 months	12 months	18 months
Patient background	●				
Albuminuria level in a first-morning void	●			●	●
Albuminuria level in a spot urine			●		
Physical parameters	●		●	●	●
Medication therapy	●	●	●	●	●
Blood test	●	●	●	●	●
Dietary intake log	●		●	●	●
J-SDSCA^a^	●		●	●	●
MMAS-8^b^	●			●	●
JP-ADDQoL^c^	●			●	
All-cause death		●	●	●	●
Composite cardiovascular outcome		●	●	●	●
Composite renal endpoint		●	●	●	●
DialBetesPlus safety questionnaire				●	
Safety		●	●	●	●
DialBetesPlus usage frequency			●	●	

^a^J-SDSCA: Japanese version of the Summary of Diabetes Self-Care Activities Measure.

^b^MMAS-8: 8-item Morisky Adherence Scale.

^c^JP-ADDQoL: Japanese version of the Audit of Diabetes-Dependent Quality of Life.

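### Three weeks without data input makes a patient a dropout, a status that after randomisation only the intervention arm can acquire and whose consequence for the analysis is left unclear

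*Protocol article*

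**What the plan says.** Methods, Participants, first describes a reminder: "If 7 days passed without any input into the system, an alert was sent to encourage the patient to resume providing input". It then gives the rule: "If 3 weeks passed without a patient inputting any data, we defined the patient as a dropout". A second route follows: "Participants with whom the study team has lost contact were also treated as dropouts". The same section lists the grounds for study discontinuance separately (serious adverse event, patient request, pregnancy, physician judgment). Inactivity is not among them.

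On who has the app, Study Design says: "The intervention group used DialBetesPlus and conventional therapy for 12 months, while the control group was treated with conventional therapy alone". The section on intervention and control gives controls a home blood pressure monitor and describes no data entry for them. Before randomisation everyone tries the app: "Prior to the randomization, all enrolled patients were asked to use DialBetesPlus for 2 weeks".

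Data Collection says: "Even if the interventional treatment was discontinued, we collected as much information as possible with the consent of participants". Sample Size raises the requirement from 63 to 80 per group for ineligibility and dropouts together, without a rate. Statistical Analysis compares change in albuminuria between the groups by t test or Mann-Whitney test.

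**The concern.** A dropout definition should mean the same thing in both arms. Here a control patient can become a dropout only by losing contact, while an intervention patient can also become one by not using the app. Such a patient may still attend the study hospital and supply a 12-month first-morning urine sample. Not using the app is non-adherence to the treatment being tested, which is a different event from loss to follow-up.

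The stake is the primary comparison. Patients who lapse from a self-management app may well do worse than those who persist. If they are left out of the intervention arm, and no comparable control patients are left out, the remaining groups are no longer those formed by randomisation. The difference in albuminuria would then probably lean towards the app even if the app did nothing.

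**Working it through.** **Can the rule operate in both arms?** The reminder sentence ties input to the system. Both arms use the system before randomisation, but for 2 weeks only, which is shorter than the 3-week trigger. After randomisation only the intervention arm is described as using it. The inactivity route can therefore be met only after randomisation and only in the intervention arm.

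**What does the sample size imply about dropouts?** Inputs from Sample Size: difference 100, SD 200 mg/g creatinine, two-sided 0.05, power 80%.

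- n per group = 2 × (1.960 + 0.842)² × 200² / 100² = 62.8, so 63. The stated figure is reproduced (power at 63: 80.1%).
- Implied allowance = 1 − 63/80 = 21.25%, or 17 patients per group, for ineligibility and dropout combined.

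Adding patients for dropouts makes sense only if dropouts are expected to contribute no primary outcome. The allowance is equal in the two groups although the definition is not.

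**What would exclusion do?** The inputs are 80 per arm, SD 200 mg/g, no true effect, an intact control arm, a share d removed from the intervention arm, and a gap g in mean change between removed and retained patients (removed worse). Both d and g are assumptions, because the documents give neither.

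- Shift in the difference = d × g, because the mean of those retained differs from the full-arm mean by that amount.
- SE = 200 × √(1/(80(1−d)) + 1/80), which is 32.0, 32.5 and 33.5 for d = 5%, 10% and 20%.
- Two-sided type I error = Φ(shift/SE − 1.96) + Φ(−shift/SE − 1.96).

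| Share removed | Gap 50 | Gap 100 | Gap 200 |
|---|---|---|---|
| 5% (4 patients) | shift 2.5; 5.1% | shift 5; 5.3% | shift 10; 6.1% |
| 10% (8 patients) | shift 5; 5.3% | shift 10; 6.1% | shift 20; 9.4% |
| 20% (16 patients) | shift 10; 6.0% | shift 20; 9.2% | shift 40; 22.2% |

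Worked cell, d = 20% and g = 200: shift 0.20 × 200 = 40; SE = 200 × √(1/64 + 1/80) = 33.5; 40/33.5 = 1.19; type I error = Φ(−0.77) + Φ(−3.15) = 22.2%.

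The error rate depends on the gap relative to the SD, and the three columns are 0.25, 0.5 and 1 planning SD. The loss of numbers matters little: with 64 against 80 and no selection, power for a difference of 100 is still 84.6%. The problem is bias.

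**The case against.** A reader might infer that the rule removes inactive patients from one arm's analysis and so selects adherent users. The article does not say this. Inactivity is not a listed ground for study discontinuance, and someone who stops using the app fits the Data Collection sentence on continued follow-up. A t test or Mann-Whitney test keeps anyone with baseline and 12-month values, whatever their adherence label. Exclusion would need an analysis-set rule. None is shown, and its absence from a condensed article is not a fault. All of this stands.

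A reader might also infer that the rule hides poor engagement. It does not, because usage frequency is a listed assessment, scheduled at 6 and 12 months.

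The size can be contested too. Patients passed a use screen before randomisation ("Eligible participants were those able to use DialBetesPlus for over 7 days during the initial 2-week confirmation period") and received reminders, so few may lapse. With 5% lapsing and a gap of 50 mg/g the effect is negligible. A gap of 200 mg/g is a whole planning SD and is large beside the Table 2 baseline median of 36.4 mg/g.

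What survives is narrower. The article itself states an arm-specific rule, gives non-adherence the status of lost contact, and budgets for dropouts as lost. Whether the continued-collection sentence covers these dropouts is not resolved, since it speaks of discontinued treatment and not of dropouts.

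**Conclusion.** The point holds as a defect in a stated definition. The inactivity route to dropout is open after randomisation only to the intervention arm, it depends on adherence to the treatment under test, and its consequence cannot be settled by reading Participants, Sample Size and Data Collection together.

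Bias is conditional on exclusion, which the documents do not establish. If these patients are excluded, the illustrated shift is 2.5-40 mg/g and type I error is about 5.1-22%. The upper end needs both 20% lapsing and a one-SD gap. If they are kept in their arm with 12-month values, this bias is zero. The direction favouring the app rests on lapsed users doing worse, which is plausible but not documented.

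**What to change.** Reconcile Participants, Sample Size and Data Collection as follows.

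- Classify 3 weeks of non-input as discontinued intervention, an adherence event reported with the usage frequency already collected.
- Use one definition of study dropout in both arms: withdrawal of consent or loss of contact.
- State that inactive patients stay in their allocated arm in the primary comparison, using their 12-month first-morning void whatever their app use.
- Label any analysis of persistent users as supplementary.

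The cost is wording, and use of data that the article says were sought. The estimated effect may be somewhat smaller because non-users are included. Where an inactive patient's 12-month sample was not obtained it cannot be recovered, so such cases should be counted and reported.

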**Inclusion criteria**
Diagnosed with T2DMHbA_1c_ 6.5% or moreBetween 20 and 75 years of ageBP lower than 180/110 mmHgeGFR 45mL/min/1.73m^2^ or moreTwo detected instances of microalbuminuria (30-299 mg/g creatinine) in spot urine samples prior to study enrollmentBMI of 22 kg/m^2^ or moreNo history of severe hypoglycemia requiring additional medical supportNo history of the following symptoms indicating hypoglycemia within the last 3 months: palpitations, tremors, dizziness, anxiety, loss of consciousness, sweating, facial pallor, tachycardia, headache, sleepiness, blurred vision, or convulsionsRegular patients of hospitals listed in Textbox 1Signatories of the informed consent form
**Exclusion criteria**
Use of cardiac pacemakerHyperthyroidism diagnosis, under medication other than thyroid hormone supplementation in the last yearMedical instability or exercise restriction as ordered by a physician, with autoimmune, heart, liver, digestive, neurological, or respiratory diseaseHb less than 10 g/ dLAlbumin 3.0 g/dL or lesseGFR less than 45mL/min/1.73m^2^Those with preproliferative diabetic retinopathy within one year of signing consent formsInability to exercisePregnancy, potential planned pregnancy, or lactatingParticipation in other clinical trialsUnder a diet that restricts proteinJudged as ineligible by doctor’s discretion for other reasons

### Design of DialBetesPlus

The details of the DialBetesPlus system are shown in Figure 2. Patients measured blood glucose, blood pressure (BP), body weight, and pedometer counts at home. The data were transferred from each device to a smartphone by either Near Field Communication (NFC) or Bluetooth, and then immediately sent to a server, where they were automatically evaluated following the Japan Diabetes Society (JDS) guideline’s target values [19]. Optimal values include blood glucose below 110 mg/dl before breakfast and 140 mg/dl at bedtime, BP below 125/75 mmHg, and pedometer counts above 8000 steps per day. DialBetesPlus determined if each reading satisfies the JDS guideline requirements and immediately sent the results to the patient’s smartphone. Patients also entered the contents and quantity of their meals and the type and duration of exercise not counted by a pedometer. Then, their intake and consumed calories were automatically calculated and sent to the smartphone along with specific advice regarding lifestyle modifications based on JDS guidelines. Critical values with blood glucose levels above 400 mg/dl or below 70 mg/dl, systolic BP above 220 mmHg, or diastolic BP above 110mg were automatically reported to the research team, and the team informed attending doctors when necessary.

**Figure 2 figure2:**
[figure not shown]
DialBetesPlus overview. NFC: near field communication.

### The DialBetesPlus Intervention and Control

The patients allocated to the intervention group used DialBetesPlus for 12 months. Patients in the intervention group receive an NFC-enabled glucometer (MS-FR201B; Terumo), a Bluetooth-enabled BP monitor (HEM-7271T; Omron), a pedometer (MT-KT02DZ; Terumo), and a scale (HBF-255T; Omron). These devices were all paired with a single provided smartphone (Arrows F-02H; Fujitsu or Galaxy Note3 SC-01F; Samsung) that transmits readings to the DialBetesPlus server via a wireless network. In addition, as a part of standard therapy, the participants in the control group were provided with sphygmomanometers to measure BP at home.

In this study, we divided the participants into 2 models (a hospital-led model and a pharmacy-led model) depending on the location of study enrollment. In the hospital-led model (the University of Tokyo Hospital, Yokohama City University Hospital, Saiseikai Yokohamashi Nanbu Hospital, and Fujisawa City Hospital), the instructions included guidance on DialBetesPlus use provided by health care providers at the patient’s hospital. In a pharmacy-led model (run by the other 4 hospitals), instructions on using DialBetesPlus were provided by pharmacists supporting the study. The pharmacists are Nihon Chouzai Co, Ltd employees, with whom we signed a business cooperation contract to conduct the pharmacy-led model portion of the study.

### Sample Size

The primary outcome of this study is a change in albuminuria levels at 12 months. We estimated that baseline first-morning-void albuminuria level would be 200 plus or minus 200 mg/g creatinine and hypothesized the difference in the change in albuminuria between the intervention group and the control group at 12 months would be 100 plus or minus 200 mg/g creatinine. Based on previous reports [20,21], we calculated 63 patients were required in each group to achieve a 2-sided significance level of .05 and a statistical power of 80%. Factoring ineligibility and dropouts, we calculated a final target number of 80 patients per group.

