**Laboratory test, median (Q1-Q3)**										
	Fasting plasma glucose (mg/dL)	144.0 (124.0-174.0)		139.0 (124.0-159.0)		150.0 (123.0-185.0)		.37		
	HbA_1c_^b^ (%)	7.5 (7.0-8.0)		7.4 (6.9-7.9)		7.5 (7.1-8.1)		.31		
	LDL^c^ cholesterol (mg/dL)	99.0 (78.0-117.0)		106.0 (78.0-117.0)		98.0 (83.0-112.0)		.55		
	HDL^d^ cholesterol (mg/dL)	49.5 (42.9-60.8)		49.0 (44.0-60.8)		50.0 (42.0-60.5)		.64		
	Triglycerides (mg/dl)	155.5 (100.0-261.0)		149.0 (100.0-261.0)		158.0 (100.0-252.0)		.64		
	Creatinine (mg/dL)	0.78 (0.65-0.92)		0.82 (0.68-0.93)		0.78 (0.62-0.92)		.33		
	eGFR^e^ (mL/min/1.73m^2^)	72.0 (61.8-85.3)		71.0 (63.8-83.0)		76.5 (59.5-85.5)		.29		
	UACR^f^ (mg/gCr)	36.4 (15.1-76.2)^g^		32.3 (14.8-70.6)		41.0 (15.1-78.0)		.49		

^a^BP: blood pressure.

^b^HbA_1c_: glycated hemoglobin.

^c^LDL-C: low-density lipoprotein cholesterol.

^d^HDL-C: high-density lipoprotein cholesterol.

^e^eGFR: estimated glomerular filtration rate.

^f^UACR: urine albumin-to-creatinine ratio.

^g^One case had a missing value.

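### The sample size assumes a baseline albuminuria of 200±200 mg/g and a 100 mg/g group difference; the trial's own baseline table does not support either, so the stated 80% power cannot be relied on for the enrolled population

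*Protocol article*

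**What the plan says.** The Sample Size section of the protocol article gives the planning values. For the baseline: "We estimated that baseline first-morning-void albuminuria level would be 200 plus or minus 200 mg/g creatinine". For the effect, the difference in change "between the intervention group and the control group at 12 months would be 100 plus or minus 200 mg/g creatinine". The result is "we calculated 63 patients were required in each group", chosen "to achieve a 2-sided significance level of .05 and a statistical power of 80" percent, then raised to 80 per group for ineligibility and dropout. The inputs are attributed to previous reports.

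The Participants section describes who may enter: "Eligible participants had T2DM with microalbuminuria (30-299 mg/g creatinine". The inclusion list specifies that this range must be found twice in spot urine before enrolment. Study Outcomes adds that patients with macroalbuminuria are not in the trial, and sets the primary outcome on first-morning-void urine.

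Table 2 gives the baseline urine albumin-to-creatinine ratio as median and quartiles: "36.4 (15.1-76.2" in all 130 patients (one value missing), 32.3 (14.8 to 70.6) in 61 controls and 41.0 (15.1 to 78.0) in 69 intervention patients. The article does not comment on the distance between these values and the assumed 200.

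**The concern.** The one operating characteristic that the article states is 80% power for an absolute difference of 100 mg/g with SD 200. It was derived for patients whose albuminuria averages 200 mg/g. The patients enrolled have a median near 36 mg/g, and most cannot fall by 100 mg/g because they do not start that high. The Discussion expects the effect to come from a decrease in the intervention group.

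At stake is how the result is read. If the 80% figure is carried into the results paper, a non-significant comparison may be taken as good evidence against a worthwhile effect. A relevant proportional reduction may look small beside 100 mg/g. Nothing in the article makes 100 mg/g a success threshold, so this is a risk of misreading and does not bias the estimate.

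**Working it through.** **1. The plan's own figure.** Inputs from Sample Size: difference 100, SD 200, two-sided 0.05, power 80%.

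n per group = 2 × (1.960 + 0.842)² × (200/100)² = 62.8, so 63. Power at 63 per group is 80.1%. The exact t-test version gives 64. With the 61 and 69 patients in Table 2, the same inputs give 81%. The stated number reproduces.

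**2. The baseline assumption against the entry range (a plausibility check).** If all values lay in 30 to 299 with mean 200, the SD could not exceed √[(299 − 200) × (200 − 30)] = 129.7. A normal distribution with mean and SD 200 puts 31% above 299 and 16% below zero; a lognormal with the same mean and SD puts 18% above 299. This is not a strict contradiction, because the entry range applies to spot urine and the assumption to first-morning urine.

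**3. The baseline assumption against Table 2.**
- Observed median over assumed mean: 36.4/200 = 0.18. A median and a mean differ in skewed data, so step 4 looks at means.
- Intervention upper quartile 78.0 is below 100. At least three quarters of that arm start at or below 78 mg/g, and none of those patients can fall by 100.

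**4. What a 100 mg/g difference would require.** If controls do not change, the mean fall in the intervention arm cannot exceed its baseline mean. The article gives no mean, so three assumed versions follow:
- Lognormal fitted to the arm's median and quartiles: log SD = ln(78.0/15.1)/1.349 = 1.217; mean = 41.0 × exp(1.217²/2) = 86 mg/g.
- The same lognormal truncated at 300: mean about 60 mg/g.
- Every patient at the top of his or her quartile, with the highest quarter at 299: (15.1 + 41.0 + 78.0 + 299)/4 = 108 mg/g. A fall of 100 would then be 100/108 = 92%.

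Under the first two, even complete disappearance of albuminuria falls short of 100. Under the third, it must nearly disappear. Otherwise controls must rise substantially.

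**5. What is known about power on the mg/g scale.** Power depends on the difference divided by the SD of change. At 61 and 69 patients, 80% power needs a difference of 2.80 × √(1/61 + 1/69) = 0.49 SDs of change. The article gives no SD of change for a population at this level. With a difference of 36.4 mg/g (the whole observed median, for illustration) and 63 per group, power is 98%, 78% or 53% for an assumed SD of change of 50, 75 or 100. It is 80% at an SD of about 73.

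**6. Detectable effect on the ratio scale.** Pooled log SD = ln(76.2/15.1)/1.349 = 1.20. Assume the same log SD at 12 months, a within-patient correlation r, and complete data in 61 and 69 patients. The ratio of geometric means detectable with 80% power, adjusting for log baseline, is

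exp[−2.80 × 1.20 × √(1 − r²) × √(1/61 + 1/69)], with √(1/61 + 1/69) = 0.1757.

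| r (assumed) | Detectable ratio | Reduction |
|---|---|---|
| 0.5 | 0.60 | 40% |
| 0.6 | 0.62 | 38% |
| 0.7 | 0.66 | 34% |
| 0.8 | 0.70 | 30% |

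**The case against.** The sum is right, and Table 2 was obtained after the plan was made. It shows that an assumption was not met; it does not show a miscalculation. That stands. The sources behind the inputs cannot be seen here, so their original justification cannot be judged.

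The entry range binds spot urine, while the assumption concerns first-morning urine. The observed lower quartile of 15.1, below the entry limit of 30, suggests that the range does not bind the baseline value. Table 2 does not name the specimen, but Table 1 schedules only first-morning urine at registration. The bound of 129.7 also concerns the baseline SD, whereas the SD of change enters the formula. For these reasons 129.7 and 108 mg/g are plausibility checks and not proofs.

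A reader might infer that the trial has no 80% power, or that it could never show its effect. The documents do not support this. A low baseline probably shrinks the SD of change as well as the difference, and 80% power survives if both shrink in proportion. Scaling the difference down to about 37 mg/g while keeping the SD at 200 gives a very low power, but it mixes a small effect with a spread that this population is unlikely to have. Nor does the article plan a 50% relative effect; it states only an absolute one. A rise in controls would also count toward the difference, although one of this size is implausible.

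Finally, recruitment and follow-up are finished, so restated power changes neither the sample size nor the estimate, and a confidence interval shows what the data exclude. This is true. It supports reporting the interval, but it does not justify leaving the 100 mg/g reference uncorrected.

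**Conclusion.** The concern holds in a limited form. The calculation is correct for its inputs, but the inputs do not describe the patients enrolled. The assumed baseline is more than five times the observed median, and the assumed effect exceeds the upper quartile of baseline in the intervention arm. These two comparisons use only figures printed in the article, and infer the specimen type from Table 1. The statement that 100 mg/g would need near-abolition of albuminuria or a large rise in controls also rests on the assumed distribution shapes in step 4.

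The 80% figure therefore cannot be relied on for this population. True power is unknown: depending on the SD of change and the effect considered, it may be lower or higher than 80%. The ratios of 0.60 to 0.70 depend on the assumed log SD of 1.2, on correlations that the article does not give, and on no loss to follow-up.

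**What to change.** Before the groups are compared:

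1. State that the 200±200 and 100 mg/g assumptions were not met at baseline, and that 100 mg/g is not the reference effect for reading the result.
2. Restate the detectable effect as a ratio of geometric means from an analysis of log albuminuria at 12 months adjusted for log baseline. Label the inputs as assumptions: log SD about 1.2 from the pooled baseline quartiles, 61 versus 69 patients, correlation 0.5 to 0.8, giving a ratio of about 0.60 to 0.70 for 80% power.
3. Add that baseline-adjusted log-scale analysis to the Statistical Analysis section, which now offers a t test or Mann-Whitney test on changes, and say how the two relate.
4. Report the effect with its confidence interval.

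The cost is a revised paragraph, one short power table and a small amount of extra analysis. No patients are added. The downside is a stated detectable effect that looks less favourable: a 30 to 40% reduction is needed for 80% power under these assumptions.
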